#### Allocation and blinding

The phases within the study will be randomized within each block (*AB* or *BA*) to minimize the risk of bias when combining the results from the individual trials [32]. The randomization will be independent of previous intervention allocations, and the package *numpy* from *python* will be used.

Due to the nature of the intervention, neither the participants nor the investigators conducting the sessions can be blinded to the assigned condition. The outcome measures are objective and automated, which reduces the potential for assessment bias.

### Measurements, effect modifiers and additional variables

2.3

#### Outcomes

The primary outcome in our study is concentration, which will be assessed through the number of correct responses from the participant on a concentration task. For that, we will use an adapted version of the Stroop test tailored for a digital environment. The Stroop test is a well-established neuropsychological assessment designed to evaluate the ability to inhibit cognitive interference and maintain selective attention [33], [34]. In our adapted Stroop test, study participants will view words displayed in different colors (see Fig. 2). When the ink color matches the word’s meaning, participants are instructed to press the key *’r’*, and the key *’w’* if they do not. The system will further record the reaction time (i.e., the time between when the word is shown until a key is pressed). This modification ensures the test is compatible with the digital setup while maintaining its ability to measure concentration and cognitive control.

For answering the secondary research questions, sensor data defined below will be used.Fig. 2Screenshots of the adapted Stroop test. The top-left corner shows the phase’s remaining time, and a gray progress bar below the word indicates the time left for the current word.Fig. 2

**(a) fig2a:**
[figure not shown]
Example, where the ink color matches the word meaning.

**(b) fig2b:**
[figure not shown]
Example, where the ink color does not match the word meaning.

#### Questionnaire data

Within the study, we will ask the participants to answer four different questionnaires *Q0*, *Q1B/Q1I*, *Q2*, and *BF-10*. *Q0* will be administered at the beginning of the study to characterize the study participants by collecting demographic variables such as gender, age, language level, and music preferences. Music preferences will be self-assessed through a multiple-choice option. If the favorite music genre, or the music genre actually used for work, is not present, participants can specify their preferences in a free-text field. In addition, the standardized *BF-10* will be used to determine the personality based on the five-factor model [35], [36]. *Q1B* will be asked after every phase to get information about the self-assessed stress and concentration level measured through a visual slider. If the phase was an intervention, the questionnaire *Q1B* would ask additionally if the participant knew the song before (yes/no/unsure) and if they liked the song (visual slider). At the end of the study, participants are asked to complete *Q2* to receive information about their personal beliefs, whether the intervention affected their concentration or not. A complete list of the questionnaires and their questions can be found in Supplementary Text 1.

#### Sensor data

In addition to questionnaire data, we will collect biomedical sensor data. We will collect continuous Electroencephalography (EEG) measurements with the *Emotiv Insight 2* sensor to assess the electrical activity of the brain and estimate, through that, the cognitive load of the individual during the phases [37]. An eye tracking sensor collects information about the movement of the eyes and the pupil’s diameter to evaluate mental stress within the study [38]. In this study, the *Tobii Pro Nano* sensor is used. Electrodermal Activity (EDA) data will be used to investigate the skin conductance, which is associated with cognitive load and stress level [5]. We collect Heart Rate Variability (HRV) and Electrodermal Activity (EDA) data through the *Shimmer3 GSR+* sensor, which can complement the analytics of the EDA data for physiological stress response [39]. The collection of diverse biomedical sensor data will enable the creation of a rich dataset to assess stress via physiological signals. The multimodal approach of collecting measurements from various sensors can help analyze cognitive load and stress. The downsides of one modality, such as the sensitivity of the pupil size to lighting conditions, can be compensated by other modalities.

The collection of sensor data is entirely voluntary, and participants may choose to opt out without affecting their participation in other parts of the study. The data will be collected through the Lab Streaming Layer (LSL) as an open-source network middleware ecosystem [40]. It will collect and synchronize the streamed sensor data. Further, a *python* script will be used to collect questionnaire data and track responses of the Stroop task. Data collected before or after the intervention and control phase, e.g., during questionnaires, will be deleted right after the recording and will not be used in any analysis.

### Participant timeline

2.4

The study will be conducted in certain steps explained in the following. An overview of the schedule of enrollment, allocation, study periods, and close-out can be found in Supplementary Table 2.

#### Study registration

Interested participants schedule an initial meeting through direct contact via email. Available time slots for onsite participation are shared, and an appointment will be scheduled.

#### Consent to study

At the beginning of the scheduled session, participants will receive a concise explanation of the study’s purpose, procedures, potential risks and benefits, data handling policies, and their right to withdraw at any time without penalty. Any questions will be addressed before participants sign the informed consent form, confirming their voluntary participation and understanding of the study. A copy of the signed consent form will be provided to each participant, and the original will be securely stored.

#### Conducting the trial

Participants will proceed with the trial, following the randomized study design explained in Section 2.2. The use of sensors is entirely voluntary, and participants may choose to opt out without affecting their participation in other parts of the study. Each trial session lasts approximately 20 min, including breaks between testing phases.

#### Discussing results and feedback session

Upon completing the trial, participants receive an overview of their preliminary results, including the preliminary results of the individual Bayesian analysis described in detail in Section 2.5. A brief feedback session allows participants to share their experiences, preferences, and impressions of the study.

### Statistical methods

2.5

#### Estimand

In order to define the estimand of interest, we specify the population, intervention, endpoint, summary, and intercurrent events following the ICH-E9 (R1) statement for estimands. The population includes all enrolled participants who start the trial. The participants are exposed in the intervention condition to music from their self-selected music genre. In the control condition, no music will be played. The endpoint is the binary outcome of each Stroop trial (correct vs. incorrect), measured repeatedly within the periods. For each participant and condition, we will summarize performance as the proportion of correct responses. The estimand of interest is the population-level average effect of music on concentration, estimated as the average across participants of the within-participant differences in the Stroop proportions between music and no-music periods. Additionally, we are interested in individual-level intervention effects, estimated as within-participant differences in the primary outcome between music and no music conditions. Missed responses are counted as incorrect; besides that, no intercurrent events are expected.

#### Primary analysis

To estimate the population-level estimand of interest, we will use a Bayesian generalized linear mixed model (GLMM). The model will include a fixed effect for condition (music vs. no music) and a participant-specific random intercept to account for baseline differences in performance. Hence, it will account for the repeated binary outcomes within participants and individual differences in baseline performance. We will use weakly informative priors to regularize estimates and make prior assumptions explicit. The posterior distribution of intervention effect will be summarized by posterior means/medians, 95% credible intervals, and posterior probabilities (e.g., $\mathrm{Pr}\left(\beta_{1}>0|\text{data}\right)$). Marginal risk differences and odds ratios will be derived from posterior predictive simulations to facilitate interpretation on both the probability and odds scales.

More formally, let $y_{ij}=1$ denote the correct answer in the Stroop task j for individual i and $y_{ij}=0$ denote a wrong answer, respectively. This will be drawn from a Bernoulli distribution with the corresponding probability $p_{ij}$: (3)$$y_{ij}∼\text{Bernoulli}\left(p_{ij}\right)$$

We will use a logistic link, and a fixed effect for the condition $A_{ij}$, where $A_{ij}=1$ denotes listening to music and $A_{ij}=0$ denotes not listening to music, respectively. Further, we will include a random intercept $b_{i}∼N\left(0,\sigma_{b}^{2}\right)$ for each participant i drawn from a normal distribution. (4)$$\text{logit}\left(p_{ij}\right)=\beta_{0}+\beta_{1}\cdot {\text{A}}_{ij}+b_{i}$$

We will use non-informative Priors for the β coefficients following a normal distribution and for $\sigma_{b}^{2}$ a half-student-t distribution with a degree of freedom of 3 and a standard deviation of 1. For the intercept $\beta_{0}$, we choose a large standard deviation to allow a high flexibility: (5)$$\beta_{0}∼N\left(0,5^{2}\right)$$$$\beta_{1}∼N\left(0,1\right)$$$$\sigma_{b}^{2}∼\text{Half-student-t}\left(v=3,\sigma^{2}=1\right)$$

To assess the robustness of the findings, sensitivity analyses are planned. First, as a non-parametric robustness check, we will perform Fisher’s exact test on aggregated counts of correct versus incorrect responses under music and no-music conditions, which provides a simple benchmark for differences between music and no-music conditions, assuming independence of observations. Next, we will include chronological time in the Bayesian generalized linear mixed model (GLMM) with uninformative priors ($\beta_{i}∼N\left(0,1\right)$), as a proxy for time-varying effects of factors such as fatigue or learning. From the fitted models, we will report odds ratios with 95% credible intervals and compute average marginal risk differences for interoperability.

If a value of $y_{ij}$ is missing (e.g., the participant did not respond within the given time frame), it will count as incorrect and be coded as 0. In the case that multiple consecutive values are missing, the length of the missing data will be reported.

In addition to the population-level estimates, we will estimate individual-level intervention effects by contrasting within-person differences in accuracy between music and no-music conditions for each participant across their trial periods. To illustrate this, we will follow the Independent Bayes Approach (IBA) described in Hoffmann et al. [41], presenting participant-specific estimates, visualizations, and posterior probabilities of benefit where appropriate. These analyses will help to characterize heterogeneity in individual responses to the intervention. For the analysis, we will use aggregated counts of the correct answers of the Stroop task.

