### Objectives

1.1

This study investigates the effect of music on concentration through a rigorous experimental design, assessing individual changes in attention levels. By including various music genres chosen by the study participants, this study will contribute to understanding the role of music in cognitive performance, ultimately providing insights into whether and potentially how music can enhance concentration.

The study addresses one primary and two secondary research questions.

•*Primary research question:* Does listening to music from a self-selected genre influence cognitive task performance compared with a no-music condition, on average on the population level and for how many individual participants?

Secondary research questions:

1.To what extent can physiological sensor data (e.g., Electroencephalography (EEG), Heart Rate Variability (HRV), Electrodermal Activity (EDA), Eye Tracking) serve as proxies for concentration changes, as measured by the cognitive task?2.To what extent do between-person differences in intervention effects on cognitive task performance be explained by effect modifiers (e.g., music preference, baseline characteristics, physiological traits)?

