### Trial design

1.2

We will conduct a series of personalized N-of-1 trials comparing intervention (**A**, listen to music) and control (**B**, do not listen to music). Each study participant will select a music genre, which they believe will most positively affect their concentration. Each trial consists of two cycles, each containing two treatment periods in a block-randomized sequence of intervention period A and control period B. This yields four possible treatment sequences, *ABAB*, *ABBA*, *BAAB*, and *BABA*. Each treatment period lasts for 3 min, followed by a questionnaire and a 1-min pause. During the treatment periods, the participants perform a digital adaptation of the Stroop test.

Fig. 1Results of Sample Size Calculation.Fig. 1

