**(a) fig1a:**
[figure not shown]
Sample size calculation with fixed $\sigma^{2}=0.05$.

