#### Sample size

We estimated the required sample size (i.e., number of participants) for testing a population-level average difference in the primary outcome (Stroop test, see Section 2.3) between periods of intervention condition (self-selected music) and control condition (no-music) through simulation studies. The simulation was performed in R using lme4, with seed 123 for reproducibility. We assumed a correct answer rate of 95% in the no-music condition and 96% across all self-selected music conditions based on pilot testing of the digital version of the Stroop task. That is, we assumed a difference in correct answer rate between the conditions of 1%. We assumed 150 observations per 180-second period based on an average response rate of 1.2 s per answer. This yielded about 600 observations per participant across all four periods. Corresponding to those values, we simulated data of our binary outcome variable $Y_{ij}$ (0 = incorrect response, 1 = correct response) for patient i at time point j (subsequently numbered throughout all periods) with a generalized linear mixed model (GLMM) using an intercept of $\beta_{0}$, a fixed effect $\beta_{1}$ of treatment $A_{ij}$ (0 = control condition, 1 = intervention) and we assumed a random effect $u_{i}∼N\left(0,\sigma_{u}^{2}=0.05\right)$ for each individual: (1)$$\beta_{0}=\mathrm{logit}\left(0.95\right)$$$$\beta_{1}=\mathrm{logit}\left(0.96\right)-\mathrm{logit}\left(0.95\right)$$$$p_{ij}={\mathrm{logit}}^{-1}\left(\beta_{0}+\beta_{1}\cdot A_{ij}+u_{i}\right)$$$$y_{ij}=\text{Bernoulli}\left(p_{ij}\right)$$

We simulated 5000 series of N-of-1 trials for each of the following number n of participants: n∈[15,16,…,29,30]. We used a fixed treatment effect $\beta_{1}$, random effect $u_{i}$, and the outcome was randomly drawn from a Bernoulli distribution as shown in Eq. (1). The seed was set to ‘123’.

Next, for each n, we analyzed each of the 5000 series of N-of-1 trials using the generalized linear mixed model (GLMM) defined in Section 2.5. For each n, we estimated the power as the ratio of p-values of the Wald z-test for $\beta_{1}$ that were <0.05 across the 5000 series of trials and calculated the 95% confidence interval for the estimated power based on the Monte Carlo error of the estimated power: (2)$${\text{CI}}_{\text{upper}/\text{lower}}=\text{Power}\pm 1.96\cdot \sqrt{\frac{\text{Power}\cdot \left(1-\text{Power}\right)}{5000}}$$

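### The primary question asks for how many participants music has an effect, but no counting rule is given, and separate per-person posteriors from about 300 items per condition cannot support a reliable count at the planned effect

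*Protocol article*

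**What the plan says.** Section 1.1 (Objectives) words the primary question as whether music influences performance "on average on the population level and for how many individual participants". The number of individuals affected is therefore part of the primary question.

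Section 2.5 deals with the individual part in four places:

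- **Estimand:** the population average is the estimand of interest. Individual effects, defined as within-person differences, are an additional interest.
- **Primary analysis, Eq. (4):** the mixed model has one common music effect and a random intercept per participant. It yields no person-specific effect of music.
- **Primary analysis, last paragraph:** individual effects come from an independent Bayesian analysis per participant on aggregated correct counts, "presenting participant-specific estimates, visualizations, and posterior probabilities of benefit where appropriate". These analyses are meant to characterise heterogeneity of response.
- **Interim analysis:** credible intervals are added for individuals.

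None of these gives a posterior-probability cut-off, an interval rule or a minimum difference that makes a participant count as influenced.

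**The concern.** A primary question that asks for a number needs a rule that produces the number. Without one, the same data give very different answers depending on where the line is drawn after results are known.

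The method matters as well as the missing line. Independent analyses do not separate sampling error from true differences between people. If each person's estimate is noisier than the effect sought, the estimates will spread widely whatever the truth. The trial could then describe participants who are helped and not helped when much of that pattern is chance. This bears directly on the article's personalised aim, and the Discussion encourages the reading by calling within-participant comparisons meaningful.

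**Working it through.** **Inputs (sections 1.2 and 2.1)**

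- Design: "Each trial consists of two cycles, each containing two treatment periods", so two music and two no-music periods per person.
- "We assumed 150 observations per 180-second period", giving 2 × 150 = 300 items per condition. The article confirms the total: "This yielded about 600 observations per participant across all four periods".
- "We assumed a correct answer rate of 95% in the no-music condition and 96% across all self-selected music conditions".
- 23 participants. Power is the share of Wald p-values "that were <0.05 across the 5000 series of trials"; a two-sided test is assumed.

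**The plan's own figures**

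*Population power.* With 23 × 300 = 6,900 items per condition, a two-proportion formula gives 80.9%. Simulation from Eq. (1) with intercept variance 0.05 and a participant-stratified test gives 81.6%. The article states 81.3%, so the inputs are understood correctly.

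*Individual precision.* The article states a 95% interval width of 0.117 for one person.

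- Risk-difference scale: SE = √(0.95·0.05/300 + 0.96·0.04/300) = √(0.0859/300) = 0.0169, or 1.69 points. Width = 3.92 × 0.0169 = 0.066.
- Log-odds scale: effect = logit(0.96) − logit(0.95) = 0.234. SE = √(1/14.25 + 1/11.52) = 0.396. Width = 3.92 × 0.396 = 1.55.

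The stated 0.117 matches neither. The article writes it for the log-odds coefficient, where it would need about 53,000 items per condition.

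**What this means for one person**

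- The standard error is 1.69/1 = 1.7 times the planned effect.
- If everyone gained exactly 1 point, the central 95% of individual estimates would still run from 1 − 1.96 × 1.69 = −2.3 to 1 + 1.96 × 1.69 = +4.3 points.
- By exact binomial enumeration, a person who truly gains 1 point scores worse with music 24% of the time and ties 7% of the time.
- Two-sided power for one person is 8.5%.

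**What this means for the count**

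The article gives no prior for the individual analysis, so flat Beta(1,1) priors are assumed. For each person, Pr(benefit) = Pr(p_music > p_control | data), with independent posteriors Beta(1 + correct, 1 + incorrect). Pass probabilities come from summing over all binomial outcomes with 300 items per condition. The count is then binomial with 23 participants. Expected counts use unrounded probabilities, and brackets give 95% ranges.

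| Cut-off for Pr(benefit) | Nobody benefits | All gain 1 point | Power of a 5% test on the count |
|---|---|---|---|
| 0.5 | 10.6 (6–15) | 15.8 (11–20) | 57% |
| 0.8 | 4.6 (1–9) | 9.1 (5–14) | 60% |
| 0.9 | 2.2 (0–5) | 5.4 (2–10) | 46% |
| 0.95 | 1.1 (0–3) | 3.1 (0–7) | 38% |
| 0.975 | 0.5 (0–2) | 1.9 (0–5) | 29% |

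The test is one-sided. Because the count is discrete, its attained level is 1.6% to 2.6%.

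Two further checks:

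- *Uniform effect or mixture.* If 11 people gain 2 points and 12 gain nothing, the expected count is 15.2 at cut-off 0.5 (against 15.8 for all +1 point) and 4.2 at 0.95 (against 3.1). Across the cut-offs the two distributions overlap by 72% to 90%.
- *Sensitivity.* With 200 to 400 items per condition, the chance that a true 1-point gainer passes 0.95 is 0.11 to 0.16. With a 90% baseline it is 0.11.

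**The case against.** **The population average is the main estimand.** The individual analysis is presented as additional and illustrative, and credible intervals will display the imprecision. That stands, and it limits how much weight the count carries. It does not remove the count from the primary question in section 1.1.

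**The rule may lie elsewhere.** A cut-off might be set in an analysis plan that is not shown, or by a convention in the cited approach. That is possible. Still, this article poses the question, names the method and qualifies its output only by appropriateness. The imprecision also remains under any cut-off.

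**The count is not empty of information.** A reader might infer from the table that the count is mostly noise and cannot tell universal benefit from none. The figures do not support that. At any one fixed cut-off, a trial in which all gain 1 point shows a higher count than a no-effect trial in 81% to 94% of pairs (ties counted half). The no-effect expectation is about two thirds of the universal-benefit count at 0.5 but only about a third at 0.95. If everyone gained 2 points, the counts would separate clearly at the lower cut-offs: 20.1 against 10.6 at 0.5, and 15.2 against 4.6 at 0.8. The supportable statement is that the count does not separate the two reliably at the planned effect.

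**Partial pooling does not make the count precise.** This also stands. A normal-approximation simulation used the log-odds SE of 0.396, a N(0,1) prior on the mean effect, and a half-t(3) or half-normal(0.5) prior on the slope SD. The posterior count averaged about 20 of 23 (interval about 14 to 23) if all gain 1 point and about 11 (about 1 to 22) if none do. For the mixture above it averaged about 19. The gain is an honest interval, not a sharp answer.

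**Conclusion.** The point holds in this form. The count is part of the primary question, sections 1.1 and 2.5 give no rule for it, and the method named for individuals leaves it strongly dependent on a cut-off that could be chosen afterwards. Universal 1-point benefit could be reported as about 2 of 23 (cut-off 0.975) and no effect as about 11 of 23 (cut-off 0.5). With a cut-off fixed in advance, the count separates these two truths with a power of only 29% to 60%. The spread of independent estimates cannot be read as heterogeneity.

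These sizes rest on the article's 95% and 96% rates and 300 items per condition, on flat individual priors, and on independent items within a person. The conclusion is about the planned 1-point effect; larger effects would separate better. The population-level analysis and its power are not in question here.

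**What to change.** 1. Add a participant-specific random slope for condition to the model in Eq. (4), with a stated prior on its standard deviation. This is a new term: the planned model has a random intercept only, and the planned time and interaction terms do not supply a slope.
2. From that model, report the slope SD, the shrunken individual risk differences, and the posterior mean and 95% interval of the number of participants with an effect above 0 and of the number below 0.
3. If individuals are also flagged, fix one cut-off before data are seen and print beside the observed count the number expected under no effect.
4. Keep the independent per-person analyses as descriptive feedback, and state that their spread is not evidence of heterogeneity.
5. Correct or explain the individual interval width of 0.117 in section 2.1, because it hides the imprecision.

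The cost is one model term, one prior and some wording; no extra data or participants are needed. The downsides are that individual estimates are shrunk towards the mean, and that the interval for the count will be wide (about 1 to 22 of 23 if there is no effect) and will still barely separate a uniform effect from a mixture.
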